## Abstract

**Background:**

Therapy for stroke prevention in older persons with atrial fibrillation (AF) is underutilized despite evidence to support its effectiveness. To prevent stroke in this high-risk population, antithrombotic treatment is necessary. Given the challenges and inherent risks of antithrombotic therapy, decision-making is particularly complex for clinicians, necessitating comprehensive risk:benefit assessments. Targeted interventions are urgently needed to support clinicians in this context; the Computerized Antithrombotic Risk Assessment Tool (CARAT) offers a unique approach to this clinical problem.

**Methods/design:**

This study (a prospective, cluster-randomized controlled clinical trial) will be conducted across selected regions in the state of New South Wales, Australia. Fifty GPs will be randomized to either the ‘intervention’ or ‘control’ arm, with each GP recruiting 10 patients (aged ≥65 with AF); target sample size is 500 patients. GPs in the intervention arm will use CARAT during routine patient consultations to: assess risk factors for stroke, bleeding and medication misadventure; quantify the risk/benefit ratio of antithrombotic treatment, identify the recommended therapy, and decide on the treatment course, for an individual patient. CARAT will be applied by the GP at baseline and repeated at 12 months to identify any changes to treatment requirements. At baseline, the participant (patients and GPs) characteristics will be recorded, as well as relevant practice and clinical parameters. Patient follow up will occur at 1, 6, and 12 months via telephone interview to identify changes to therapy, medication side effects, or clinical events.

**Discussion:**

This project tests the utility of a novel decision support tool (CARAT) in improving the use of preventative therapy to reduce the significant burden of stroke. Importantly, it targets the interface of patient care (general practice), addresses the at-risk population, evaluates clinical outcomes, and offers a tool that may be sustainable via integration into prescribing software and primary care services. GP support and guidance in identifying at risk patients for the appropriate selection of therapy is widely acknowledged. This trial will evaluate the impact of CARAT on the prescription of antithrombotic therapy, its longer-term impact on clinical outcomes including stroke and bleeding, and clinicians perceived utility of CARAT in practice.

**Trial registration:**

Australian New Zealand Clinical Trials Registry: ACTRN12613000060741.

## Background

### Age, atrial fibrillation, and stroke

Stroke accounts for significant morbidity and mortality globally every year, including in Australia (where this study is being conducted) [1]. Advancing age is a key non-modifiable risk factor for stroke, and this is important to recognize given that 80% of stroke sufferers are over 60 years old and that 80% of stroke-related deaths occur in those over 75 years old [1]. As the population ages the incidence of stroke rises, doubling the disability burden by the year 2031 [2].

Atrial Fibrillation (AF), commonly dubbed the ‘a*rrhythmia of the millennium*’, is the commonest irregular heart rhythm encountered in clinical practice, and is reportedly most prevalent in the elderly population [3,4]. It is infamous for its propensity to form stroke-causing thrombi in the heart chambers (atria) that can embolize to other parts of the body; these thrombo-emboli can subsequently occlude the blood vessels and disrupt the circulatory supply through to the brain, causing ischemia, i.e., stroke [5].

Patients with AF have at least a 5 to 6-fold increased risk of stroke [6], and in the elderly the proportion of stroke attributable to AF is at least one-third [7-9]. Independently, ‘old’ age and chronic AF are major risk factors for stroke but, unfortunately, both are irreversible. This complex of factors significantly compounds the risk of stroke in older people with AF, and for this reason, stroke prevention in this population is now recognized as a global health priority.

### Stroke prevention therapy

To date, numerous large clinical trials and meta-analyses have provided convincing evidence that antithrombotics (anti-clotting agents) can prevent stroke in patients with AF [10,11]. Historically, antithrombotic therapy has been reliant on two key agents: warfarin (anticoagulant) and aspirin (antiplatelet). Warfarin has been reported to reduce the risk of stroke by approximately two-thirds, whilst aspirin is less effective, reducing the risk by about 20% [10].

### Underutilization of preventative therapies

Although highly effective antithrombotic medicines, specifically warfarin, are significantly underutilized in practice [12-16]; data from local Australian practice shows that this is especially true in the target at-risk older population, even in the absence of apparent contraindications [12]. A fear of side effects underpins this [17,18] because antithrombotics inherently increase the potential for bleeding. Therapy, therefore, requires careful patient selection, close patient monitoring (via blood tests), and regular dosage adjustment. This is particularly true for warfarin, as pharmacological characteristics render its use more challenging in patients with multiple medical comorbidities and/or polypharmacy (e.g., elderly) [19].

Unfortunately, the inconvenience of therapy has led some clinicians to cite “old age” *per se* as a contraindication to treatment without further risk/benefit assessment, leading to the underutilization of warfarin. In older people the risk of stroke is high but so too may be the risk of medication misadventure [20], giving clinicians a platform to question whether initiating life-saving anti-coagulant therapy is done at the expense of causing potentially life-threatening side-effects.

In more recent times, clinicians have been awaiting the availability of alternative agents (so-called ‘novel’ oral anticoagulants - NOACs) to overcome some of these known challenges of warfarin therapy. Whilst the newer agents present viable, effective treatment alternatives (e.g., dabigatran, rivaroxaban, apixaban), they are not without their own inherent risks [21]. Furthermore, the cost-effectiveness of these agents must be carefully considered, before widespread use in the at-risk population can be supported. For this reason, decision-making regarding stroke prevention in AF is still largely focused on the selection of warfarin (anticoagulant) versus aspirin (antiplatelet) therapy, and has been highlighted again in the recent Australian Government Review into Anticoagulation Therapies for Atrial Fibrillation [22]. In any case, the expanding armamentarium of treatment options for stroke prevention in AF has added to the complexity of decision-making in this clinical context.

### Optimizing stroke prevention in general practice

Primary care is the key to optimal stroke prevention, and past guidelines have stated that “*General Practitioners … are the key to better stroke prevention. What is needed is proactive opportunistic screening and risk management, and prompt action for two groups of patients: those with stroke/TIA symptoms and those with atrial fibrillation*” (National Health and Medical Research Council, NHMRC; (23)).

Although it is widely recognized that general practitioners (GPs) are well placed to facilitate stroke prevention [23], the EXAMINE-AF study conceded that management by a GP, compared to a cardiologist, continues to be a significant predictor for the underutilization of warfarin, even in high-risk patients with a prior history of stroke [24]. A national survey of Australian GPs reinforces that there is a need to support GPs in quantifying stroke risk versus bleeding risk, to eliminate misperceptions about risk and to reduce anxiety about “*acts of commission*” [18]. Careful patient selection via risk/benefit assessment is integral to decision-making here, but guidelines *per se* are ineffective as they fail to demonstrate how evidence can be actioned in individual patients [13,25].

In a previous study, it has been shown that an applied comprehensive risk assessment process can significantly improve the utilization of therapy [26]. Using evidence-based algorithms to facilitate the systematic review of individual stroke risk and bleeding risk (taking into account medical, functional, cognitive, medication-related, and social factors), the use of antithrombotics increased (59.6% versus 81.2%, p < 0.001). Overall, 36% of patients required changes to their existing therapy, with 76.9% of these being ‘upgrades’ to more effective treatment. Following the success of this intervention, the founding risk assessment algorithm has been integrated into a key Clinical Indicator (Indicator 1.6) in the NSW Therapeutic Advisory Group’s (TAG) “*Indicators for Quality Use of Medicines in Australian Hospitals”*[27].

Although highly effective, a limitation of the above approach is the reliance on a paper-based process that cannot be linked into an increasingly electronic and online health system. In response to clinician feedback, the CARAT, an electronic (web-based) Computerized Antithrombotic Risk Assessment Tool, has been developed to aid clinicians in selecting appropriate antithrombotic therapy in older persons with AF. Unlike paper-based guidelines, it facilitates a systematic review of risk factors and calculates the estimated risk versus benefit of therapy in an individual patient. The CARAT inputs are modeled on those used in a previous study [26] and current evidence [28].

An exploratory study has yielded feedback from clinicians highlighting the potential utility of CARAT in practice [29]. Overall the majority of clinicians: are satisfied with CARAT’s format (94%); agree with its recommendations when applied to patient cases (72%); and agree with its estimate of stroke and bleeding risk (>66%). Most (63%) clinicians (geriatricians, cardiologists, neurologists, hematologists) positively indicated that CARAT was at least “*somewhat useful*” for their clinical practice with 22% indicating it was ‘very useful’ because:

“Highlights functional elements that need to be considered. Multifactorial review is essential”

“Warfarin is not a lifelong decision; people can fail a trial of anticoagulation but embolic stroke is irreversible [this tool helps re-focus away from bleeding risk, highlights stroke risk]”

“May be useful for a less experienced doctor”

“This tool should ideally be applied in ED and result should go to local medical officer”

“Rapid calculation of risks is very useful”

“Bleeding risk assessment section is very useful”

Whilst these findings are encouraging, the utility of the tool is expected to be far greater in general practice given its focus on chronic disease prevention and management, and where previous studies have highlighted a poor dissemination of evidence to support GPs’ decision-making [17]. Indeed, there is scope for improving the use of therapy through such a tool; preliminary data evaluating the CARAT as a screening tool shows that, in a cohort of older patients (≥65 years) with AF, less than half (44%) of those indicated for warfarin (N = 126) were prescribed it; in those in whom warfarin was NOT indicated (i.e., unfavorable risk: benefit profile), 46% of patients *were* actually prescribed it. Furthermore, 12% of patients did not receive any preventative therapy at all, despite it being indicated and the absence of contraindications (30). The National Institute of Clinical Studies acknowledges our earlier findings and those of others, supporting the crucial need for improving stroke risk assessment and provision of information to GPs [30].

### Study aim and objectives

Optimizing stroke prevention in general practice requires targeted interventions to address the critical need for improving stroke risk assessment and provision of information to GPs [30]. Therefore, this study will undertake a trial of the CARAT in general practice as a targeted intervention to assist clinicians in selecting appropriate therapy for stroke prevention in older persons with AF.

The **Specific Objectives** of this study are to:

1. evaluate the impact of CARAT on the prescription of antithrombotic therapy post-application of the tool, including initiation of, and changes to, therapy (quantitative data analysis)

2. measure the longer-term impact of CARAT on clinical outcomes (strokes, bleeds) (quantitative data analysis)

3. gauge clinician feedback regarding CARAT in terms of its perceived utility in practice (qualitative data analysis)

### Hypotheses

Application of the CARAT in general practice will improve the utilization of appropriate antithrombotic (anti-clotting) therapy in older persons with AF. Further, it will improve clinical outcomes in older persons with AF, specifically in terms of reducing the incidence of stroke and bleeding events.

## Methods and design

### Study design and setting

#### Design

This study is a prospective cluster-randomized controlled clinical trial (CRT) utilizing an innovative online practice tool, i.e., the Computerized Antithrombotic Risk Assessment Tool - CARAT (Trial Registration: ACTRN12613000060741). Approval for the conduct of the study has been granted by the Human Research Ethics Committees of the participating institutions: University of Technology Sydney; University of Sydney; and University of Newcastle. Additionally, support from the participating Divisions of General Practice has also been granted: Hunter Urban (i.e., GP Access), Hunter Rural, Central Coast, and Hornsby Ku-ring-gai divisions.

#### Setting

The study will be conducted in Australia, in the state of New South Wales (NSW). Specifically, the study will be undertaken within 4 Divisions of General Practice that accommodate a high proportion of older patients and which represent persons from diverse backgrounds in terms of socioeconomics, health status, and access to health services: City-Metropolitan (Northern Suburbs), Coastal-Region (Central Coast, NSW), Regional-Urban (Hunter Region, Newcastle metropolitan area), and Regional-Rural (Hunter Region, rural areas).

### Participants

Fifty GPs will be recruited and randomized to either the intervention (CARAT) arm or control (usual care) arm to recruit a total 500 elderly patients with AF (Figure 1), i.e., 25 GPs will be recruited to each of the two study arms. Randomization will occur at the GP level at the time of recruitment [31], not at the division or regional level, to facilitate comparison over a cross-section of GPs and patients, and to negate any regional confounders.

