### Participant recruitment and eligibility

a) General Practitioner

GPs will be recruited via invitational letters, promotional flyers inside newsletters, and presentations during education events, coordinated by the Divisions of General Practice. Eligible GPs include those who:

•are practicing in one site at a general practice surgery and not across multiple sites or surgeries;

•practice in the specified Divisions of GP;

•provide informed written consent to participate in the study.

Once recruited, the GPs will be randomly allocated to a study arm (‘intervention’ versus ‘control’) using computer-generated random allocation number sequences. The process will be coordinated centrally by a Chief Investigator independently of GP recruitment, intervention implementation, or data collection processes, and who will conceal the initial allocation process from project officers (e.g., allocation numbers will be placed in sealed, serially coded envelopes, and housed in a locked cabinet).

b) Patient

Patients will be recruited by their GPs during routine care over a 3-month period. Each GP will be required to recruit 10 patients that meet the following study inclusion criteria:

•are aged ≥ 65 years;

•have a diagnosis of chronic (persistent) AF, whether new or pre-existing and irrespective of the antithrombotic therapy prescribed at the time of recruitment;

•provide informed written consent to participate in the study and agree to be followed-up via telephone interview over a 12 month period (1,6 and 12 months).

Patients will be informed that all personal information is de-identified and that they may withdraw from the study at any time without any negative consequences.

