In using the cluster-randomized trial design, contamination *within* groups of GPs is minimized. Any contamination *between* groups will be minimized through specific screening during the recruitment process to exclude those GPs practising across multiple (≥1) surgeries. Within ‘group’ practices (e.g., medical centres where more than 1 GP is employed), all participating GPs will be allocated to the same study arm (block randomisation). Once allocated, drop-ins between arms and sharing of the ‘intervention (i.e., password protected CARAT) will not be permitted.

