### Data collection

In addition to the output generated by CARAT, purpose-designed data collection instruments (record forms, surveys, questionnaires) will be used to extract and record specific data (Table 1). Dedicated Project Officers will be allocated to each participating division of general practice, to coordinate the conduct of the study (i.e., participant recruitment, implementation of intervention, data collection, provision of support to GPs) at each site.

**Table 1 T1:** Data collection items for GPs and patients

**GPs**	**Patients**
• Demographics (age, gender)	• Patient demographics
• Practice experience (years, specialty)	• Medical history, co-morbidities, medication
• Practice site features (location, number of clients)	• History of AF (duration, new onset or chronic)
• Decision-making processes (e.g., resources or processes normally used)	• Risk factors for stroke (per CARAT)
• Agreement with CARAT recommendations (Intervention group)	• Risk factors bleeding (per CARAT)
• Satisfaction with CARAT as a tool (Intervention group)	• Quality of life (e.g., SF36)
• Barriers to prescribing therapy (ALL GPs)	• Risk factors for medication misadventure [25]
	• Current antithrombotic therapy utilised
	• History of clotting and bleeding events
	• Health services used to support therapy
	• Health services used to support therapy

Baseline data for patients and GPs will be collected by the project officer within 48 hours of the index consultation. During the baseline visit, the GP will apply CARAT to consecutive admissions over a period of 3 months and obtain the patient’s consent to participate. GPs will print-out the completed risk-assessment template (generated by the CARAT) for subsequent review by the project officer. Each GP will then ‘flag’ the patient for review and baseline data collection by the project officer by returning a purpose-designed fax-back form with basic patient details. Baseline data will be extracted from medical notes, patient interview, and a brief patient survey.

Clinical outcome data will be collected at 1, 6 and up to 12 months after the index consultation. This data will be collected from patients via follow-up telephone interview (15–20 minutes) by the project officer. To verify outcomes, the GP will be contacted via phone and/or the patient’s notes reviewed. Hospital medical records may also be reviewed where patients have been admitted for an acute event including a stroke or bleed.

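### GP-level randomisation avoids tying arm to region, but as described it does not negate regional confounders: it balances the four divisions only on average

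*Protocol article*

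**What the plan says.** All references are to the protocol article.

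- **Participants:** "Randomization will occur at the GP level at the time of recruitment", with "25 GPs will be recruited to each of the two study arms". The section gives the reason for this unit: "not at the division or regional level, to facilitate comparison over a cross-section of GPs and patients, and to negate any regional confounders".
- **Setting:** "the study will be undertaken within 4 Divisions of General Practice that accommodate a high proportion of older patients". The divisions run from metropolitan to rural and are described as covering "diverse backgrounds in terms of socioeconomics, health status, and access to health services".
- **Participant recruitment and eligibility:** allocation uses "computer-generated random allocation number sequences", run centrally by a Chief Investigator, with sealed coded envelopes.
- **Minimizing selection bias and contamination:** one restriction is described. Within a group practice, "all participating GPs will be allocated to the same study arm (block randomisation"). Blocking here means keeping a practice together, not balancing arms within a division.
- **Data collection:** "Dedicated Project Officers will be allocated to each participating division of general practice". The section on minimising bias adds that these officers deal with GPs in both arms and are no longer blind once allocation is done.
- **Data analysis:** all analyses are adjusted for clustering. Division is not named as a covariate.

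**The concern.** The Participants sentence claims a property for the design. Choosing a smaller unit of randomisation and balancing a prognostic factor are different things. Randomising GPs instead of divisions means that no division is assigned wholesale to one arm. It does not make the mix of divisions alike in the two arms when there are only about 50 units. There are fewer independent units wherever participating GPs share a practice, because those GPs move together.

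The sections on recruitment and contamination describe nothing that would produce balance by division, such as separate lists or minimisation. By the article's own account the divisions differ in ways likely to affect prescribing. Project officers are also assigned by division, so an uneven division mix is an uneven officer mix as well.

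At stake are some avoidable noise in the arm comparison, baseline tables that may show visible regional imbalance, and a sentence that readers may take as an assurance that region needs no further handling.

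**Working it through.** **Inputs from the article.** 50 GPs, 25 per arm, 10 patients each (25 × 10 = 250 per arm; 50 × 10 = 500 in all, as stated). Four divisions. ICC 0.03, drop-out up to 20%, baseline warfarin use 35%, expected gain 15 to 23 points.

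**Assumptions, not in the article.** GPs per division: near-equal (13/13/12/12) or uneven (20/14/10/6). Warfarin use by division: 25%, 32%, 38%, 45% (mean 35%).

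**Step 1: how often a division splits unevenly.** GPs are treated as independent units and allocation is unstratified, either as an exact 25:25 split or by independent tosses. A 2:1 or worse split means at least 9:4 of 13 GPs, 8:4 of 12, or 4:2 of 6. There were 10,000 simulated allocations per row; the last column is a direct count over all possible splits.

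| Division sizes | Scheme | Some division 2:1 or worse, simulated | Same, counted exactly |
|---|---|---|---|
| 13/13/12/12 | exact 25:25 | 64% | 63% |
| 13/13/12/12 | independent tosses | 80% | 80% |
| 20/14/10/6 | exact 25:25 | 78% | 78% |
| 20/14/10/6 | independent tosses | 85% | 85% |

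The uneven layout scores high largely because of its six-GP division. The chance of 4:2 or worse there is 1 − C(6,3)·C(44,22)/C(50,25) = 0.67, from one GP changing sides. A measure less sensitive to small divisions is the difference between arms in a division's share of that arm's GPs. Some division differs by 20 points or more in 27% to 43% of allocations. The largest such difference averages 16 to 17 points.

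**Step 2: what stratifying does.** With lists made within division and GPs as units, the average largest difference falls from 16–17 points to 0–3. With two-GP practices kept together it falls from 24–25 to 7–10, so some imbalance remains. The two-GP case shows direction only: practices of exactly two cannot give the stated 25 GPs per arm, since 25 is odd.

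**Step 3: effect on the arm difference.** The between-division variance of the assumed rates is (0.10² + 0.03² + 0.03² + 0.10²)/4 = 0.00545. The SD of the arm difference due to division alone is √(0.00545 × 4/50) = 0.021, or 2.1 points. Simulation over both layouts gives 2.1 to 2.3. The mean shift is zero.

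**Step 4: compare with the planned precision.** Reading 250 as patients per arm and allowing 20% drop-out leaves 200 per arm, or 8 per GP. The design effect is 1 + 7 × 0.03 = 1.21. For 35% against 50%:

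SE = √[(0.35 × 0.65 + 0.50 × 0.50) × 1.21/200] = 0.054, or 5.4 points.

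Share of variance: 2.1²/5.4² = 4.41/29.16 = 0.15.

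**Step 5: is the 2.1 points extra or already counted?** On the ICC scale the assumed spread is 0.00545/(0.35 × 0.65) = 0.024, which is 80% of the planned 0.03. The between-GP part of the 5.4-point SE is √(0.03 × 0.4775/25) = 0.024, or 2.4 points. So most of the 2.1 points already lies inside the 5.4. If it were wholly additional, the SE would be √(29.16 + 4.41) = 5.8 points. If it is wholly inside and is removed by stratifying and adjusting, the SE falls to √(29.16 − 4.41) = 5.0 points.

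**The case against.** The strongest reply is that the sentence contrasts GP-level with division-level allocation, and in that contrast it is right. Randomising four divisions would tie arm to region, and randomising GPs removes that systematic link. What is left has zero expected bias and is covered by a valid cluster-adjusted analysis, which the article promises. This stands. It limits the point to precision and to the strength of the word negate.

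Three stronger readings are tempting, and the article does not support them.

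- *That allocation is definitely unstratified and division definitely left out of the models.* This is inferred from silence in a condensed article. Saying that randomisation is not by division names the unit and leaves stratification open, and such detail commonly sits in a fuller document. The finding therefore rests on the claim that is made, not on the missing detail.
- *That project officer is confounded with arm.* Officer goes with division, not with arm. Officers work with GPs in both arms, instruments are common to both, and outcomes are to be verified with the GP or the patient's notes. Unblinded data collection is a separate matter that stratifying would not cure.
- *That division imbalance adds 2 points to the planned standard error.* Step 5 shows that most of it is already allowed for through the ICC.

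It is also fair to say that stratifying is a gain in efficiency, and that a randomised comparison without it remains valid.

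**Conclusion.** The point holds in a limited form. GP-level allocation avoids tying arm to region, but the scheme as described balances the divisions only on average, so the claim to negate regional confounders is too strong. A noticeable split in some division is more likely than not: roughly 64% to 85% for 2:1 or worse with GPs as units, and balance tends to worsen where practices contribute several GPs. The consequence is modest: an SD of about 2 points in the arm difference, about 15% of the variance behind a 5.4-point SE, against a planned effect of 15 to 23 points. These figures depend on assumed division sizes, an assumed 25% to 45% range in warfarin use, and reading 250 patients as the number per arm. The trial is not biased by this, but an inexpensive gain in precision is available.

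**What to change.** If the full protocol already stratifies by division, one sentence in the Participants section saying so is enough for the design. Otherwise:

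1. Generate a separate allocation list within each of the four divisions, using permuted blocks of the unit actually allocated (the practice, or the solo GP). A GP who joins from a practice already allocated follows that practice.
2. Include division as a fixed effect in the between-arm models, alongside the adjustment for clustering.
3. Reword the Participants sentence to say that GP-level allocation avoids tying arm to region, and that stratification and adjustment deal with the division imbalance that remains.

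The cost is four lists instead of one and three degrees of freedom in the models, with no extra patients or staff. Some imbalance will remain where practices contribute several GPs (an average largest difference of 7 to 10 points in the two-GP illustration), which is why the division term is needed as well as the stratified lists.
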